# **INTRODUCTION AND RATIONALE**

## **Background**

In this study we wish to investigate the effect of Adductor Canal Block on pain and morphine consumption in patients after revision knee arthroplasty.

Total knee arthroplasty is associated with intense postoperative pain and revision arthroplasty is assumed to be even more painful. The patient population consists primarily of elderly people with high co-morbidity. It is therefore essential that, in addition to effective pain relief and minimal side effects, the pain treatment is aimed at promoting functional rehabilitation and reducing postoperative morbidity. There exists a large number of treatment options for postoperative pain treatment after knee surgery (1). Everything from systemic opioids, NSAIDs, paracetamol and gabapentinoids, to central (epidural) and peripheral nerve blocks and local infiltration analgesia (2) is employed. No single approach has been shown to be generally effective and there is no "gold standard" (1).

The sensory innervation of the knee arises from n. femoralis, n. ishiadicus and n. obturatorius. N. saphenus is is the most important cutaneous branch of n. femoralis. It follows a. femoralis down into the adductor canal and passes through this to innervate the lower medial and anterior aspect of the knee and lower leg. A dissection study by Horner et al. has shown that the ramus anterior n. obtoratorius perforates m. adductor magnus and branches into the adductor canal (3). The branches supply the medial and anterior part of the femur, and to a large extent the perigeniculate structures.

Block of n. femoralis as well as plexis lumbalis has been shown to be effective for pain relief after knee surgery (1). The development of ultrasound-guided (ultrasonographic, US) blocks makes it possible to visualize the nerve and the spread of the local anaesthetic and thus potentially increase the success rate of peripheral nerve blocks (4).

As n. saphenus is the cutaneous main branch from n. femoralis, it is estimated that a block of this will be a good analgesic supplement to postoperative pain treatment after knee surgery. A simultaneous block of ramus anterior n. obturatorius will enhance the analgesic effect.

A number of different methods for block of n. saphenus have been described. These methods include studies with or without nerve stimulation as well as US-guided blocks (5-7). We want to investigate the effect of Adductor Canal Block by US-guided catheterization in the adductor canal at the mid-thigh level, with subsequent injection of Ropivacaine 7.5 mg/ml. The postoperative analgesic efficacy of such a block for total knee arthroplasty has not previously been described in the literature.

Adductor channel blocks are almost exclusively sensory blocks, since the ramus muscularis n. femoralis to m. vastus medialis is the only motor branch passing through the adductor canal. It is our expectation that this primarily sensory block will promote quick mobilization and reduce the risk of complications due to immobilization.

## **Aim**

Our aim is to investigate the effect of Adductor Canal Block as a post-operative analgesic treatment after revision knee arthroplasty. Our hypothesis is that Adductor Canal Block can reduce the postoperative use of morphine, as well as reduce pain scores, side effects and facilitate mobilization, when compared with placebo treatment.

## **Endpoints**

#### Primary end points

- Pain score with 45 degree active flexion of the knee (VAS) 4 hours postoperatively.

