# **STUDY SELECTION**

## **Inclusion criteria.**

Patients must meet all the following criteria to be suitable for inclusion in the study:

- Age > 40 < 85 years old
- Patients scheduled for total knee arthroplasty in general anaesthesia with Propofol and Ultiva.
- Patients who gave their written informed consent to participating in the study after having fully understood the contents of the protocol and restrictions.
- ASA 1-3.
- BMI > 18 and < 40

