## **Exclusion criteria.**

Patients who meet one or more of the following criteria are not suitable for inclusion in this study:

- Patients who cannot cooperate with the study.
- Patients who cannot understand or speak Danish.
- Patients with allergy to the medicines used in the study.
- Patients suffering from alcohol and/or drug abuse – based on the investigator's opinion.

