## **Clinical assessments**

- **Patient-controlled morphine consumption**:
  - Number of bolus doses delivered in the period 0-8 hours postoperatively is recorded
  - Number of bolus doses delivered in the period 0-24 hours postoperatively is recorded
- **Pain:**
  - Patients' pain is recorded on a Visual Analogue Scale (VAS) of 100 mm, where 0 = no pain and 100 = worst possible pain. Patients state their own pain intensity.
  - Pain is recorded at rest and in connection with 45 degrees active flexion of the knee.
  - Pain is recorded preoperatively before administration of medication, as well as 1, 2, 4, 6, 8 and 24 hours postoperatively, corresponding to the end of the trial period.
- **Side effects:**
  - Nausea and sedation are recorded on a verbal scale (none, mild, moderate, severe) 1, 2, 4, 6, 8 and 24 hours post-operatively.
  - The number of productive vomiting events (volume estimated over 10 ml) is recorded corresponding to the periods 0-1, 1-2, 2-4, 4-6, 6-8 and 8-24 hours post-operatively by interview with the patient.
  - The patient's use of Zofran (mg) 0-8 and 0-24 hours postoperatively is recorded.

The study extends for each patient from introductory conversation to 24 hours postoperatively. The patient receives the above treatments in accordance with a computer-generated randomized list.

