# **STATISTICAL ANALYSES**

## **Calculation of the number of patients**

Results from previous studies suggest that all patients will have pain postoperatively. Average pain scores (VAS) for activity (45 degree flexion of knee) in the first 24 hours based on previous studies is typically around 75 (SD 20) (8). We assess that a reduction of 20 in the pain score (VAS) will be clinically relevant.

With a type 1 failure risk of 5% and a type 2 failure risk of 20%, a total of 34 patients, i.e. 17 in each group, will be required.

It is planned to include a total of 34 evaluable patients in the measure of main effect. To compensate for drop-outs it is aimed to include 36 patients.

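### The primary endpoint has no stated value when pain stops the 45 degree flexion, and the analysis rule then drops those patients, which biases the comparison toward no effect

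*Protocol*

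**What the plan says.** - **Endpoint.** Under Primary end points the protocol names a single measure: "Pain score with 45 degree active flexion of the knee (VAS) 4 hours postoperatively".
- **How it is measured.** Clinical assessments states: "Pain is recorded at rest and in connection with 45 degrees active flexion of the knee". The scale is a 100 mm VAS, "where 0 = no pain and 100 = worst possible pain. Patients state their own pain intensity". No code, substitute movement or rule for an attempt is given for a patient who does not reach 45 degrees.
- **When.** "Pain is recorded preoperatively before administration of medication, as well as 1, 2, 4, 6, 8 and 24 hours postoperatively".
- **Who is analysed.** Data processing limits the statistical analysis to patients whose flexion pain scores for 0-8 hours are available. Evaluability is settled before the code is broken, and the trial ends once 34 evaluable patients are in.
- **Planning values.** Calculation of the number of patients takes a mean flexion score of 75 (SD 20), a relevant reduction of 20, 5% type 1 and 20% type 2 error, and 17 per group. It adds: "To compensate for drop-outs it is aimed to include 36 patients".
- **Test.** Mann-Whitney for ratio-interval data.

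**The concern.** The measure depends on the patient performing a set movement. The patients most likely to stop or refuse at 4 hours are those in most pain, and for them the protocol leaves the entry on the form to whoever is at the bedside. If the entry is blank, the analysis rule removes the patient.

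Exclusion would then depend on an outcome that arises after randomisation and that the treatment is meant to change. If ropivacaine relieves pain, fewer ropivacaine than placebo patients are lost, and those lost are the highest scorers. The placebo mean falls more than the ropivacaine mean, and the estimated benefit shrinks.

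The setting makes this plausible. The Background assumes that revision arthroplasty is more painful than primary arthroplasty, and a planning mean of 75 with SD 20 puts many placebo patients near the top of a 100 mm scale. The gap also remains if the analysis needs only the 4 hour score, because these patients have no 4 hour score.

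**Working it through.** **1. The plan's own figure.** Inputs from Calculation of the number of patients: difference 20, SD 20, two-sided 5% (sidedness is not stated and is assumed), power 80%.
- Normal approximation: n per arm = 2 × (1.960 + 0.842)² × 20²/20² = 15.7, so 16.
- Two-sample t-test (noncentral t): 17 per arm, power 80.7%.

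The stated 34 reproduces. The issue is not the sample size arithmetic.

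**2. Assumed model with a sharp cut-off.** Pain on flexion is N(75, 20) with placebo and N(55, 20) with ropivacaine, limited to 0-100. With nobody lost, the expected difference after limiting is about 19.1 mm. Suppose everyone whose pain would exceed a cut-off c fails to flex and has no score.
- Share lost = 1 − Φ((c − mean)/20).
- Mean of those left = mean − 20 × φ(z)/Φ(z), with z = (c − mean)/20. The lower limit at 0 has a negligible effect.

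| c (mm) | Placebo lost | Ropivacaine lost | Placebo mean left | Ropivacaine mean left | Difference |
|---|---|---|---|---|---|
| 85 | 31% | 7% | 75 − 10.2 = 64.8 | 55 − 2.8 = 52.2 | 12.6 |
| 90 | 23% | 4% | 75 − 7.8 = 67.2 | 55 − 1.8 = 53.2 | 14.0 |
| 95 | 16% | 2% | 75 − 5.8 = 69.2 | 55 − 1.1 = 53.9 | 15.3 |

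**3. Power, by simulation** (Mann-Whitney, two-sided 5%):

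| c (mm) | Patients left out, replaced until 34 evaluable | Same patients scored 100, 17 per arm |
|---|---|---|
| none lost | about 78% | – |
| 85 | about 56% | 76-78% |
| 90 | about 62% | 76-78% |
| 95 | about 68% | 76-78% |

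Separate runs with replacement agree within about 2 points. Replacement follows the stopping rule in Data processing. It restores the number analysed but not the missing top of the distribution.

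**4. A gentler model.** The chance of not flexing rises smoothly with pain; 18 per arm, no replacement.

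| Placebo / ropivacaine unable | Difference (mm) | Power, left out |
|---|---|---|
| 0% / 0% | 19.0 | 81% |
| 5% / 1% | 18.2 | 77% |
| 16% / 3% | 16.0 | 67% |
| 24% / 5% | 14.6 | 57% |
| 32% / 8% | 13.6 | 51% |

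Scoring the same patients 100 keeps power at 77-81% throughout.

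**The case against.** **The scale does not forbid a score.** A patient who tries to bend and stops can still mark the line, and the protocol nowhere requires the movement to be completed. This stands: the fault is an unstated instruction, and the bias arises only if such patients are recorded as missing. But the protocol itself makes a missing score a ground for leaving a patient out. If neither the attempt nor the reason for stopping is recorded, a later analysis plan cannot recover them.

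**The size is conjecture.** No cut-off or failure rate is in the documents. The planning mean of 75 is described as pain on flexion, so it may already come from patients who managed the movement, and cutting its top off may count the loss twice. This stands too, and it is why the mild scenario belongs beside the sharp ones.

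**Stronger readings that a reader might infer:**
- *Power falls to 47, 56 or 63% at cut-offs of 85, 90 or 95.* Those figures fix 17 per arm and delete patients without replacement, which contradicts recruitment until 34 are evaluable.
- *An entry criterion on knee movement is missing, and stiff knees will use up the two spare places.* Eligibility names "Patients scheduled for total knee arthroplasty in general anaesthesia with Propofol and Ultiva" and excludes "Patients who cannot cooperate with the study", with nothing explicit on range of motion. The chance of more than 2 of 36 being unable is 0.6-3.5% at an assumed 1-2% rate and 27-71% at 5-10%. But 36 is an aim and not a cap, so exceeding it means longer recruitment. Nothing in the protocol shows that stiffness before surgery persists after an operation on that joint. Excluding such patients would also narrow the population, which is a trade-off and not a correction.

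**The bias is conservative.** Under this model it works against finding a benefit and would not create a false one. That lowers the severity but does not remove the problem.

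**Conclusion.** The concern holds for scoring and analysis, not for eligibility. The protocol does not say what a flexion stopped by pain contributes to its primary endpoint, and it removes patients without flexion scores.

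The direction of the bias, toward zero, rests on three conditions: the block works, inability is caused by pain, and these patients are recorded as missing. The size cannot be fixed from the documents. It runs from a loss of about 4 power points (81% to 77%) in the mild scenario to a loss of about 10-22 points (78% to 68-56%) under sharp cut-offs with replacement.

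The gap is worth closing before recruitment because it concerns the primary measurement and costs little to repair.

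**What to change.** 1. **Clinical assessments.** Ask every patient to attempt the flexion at each scheduled time. Record whether 45 degrees was reached and, if not, whether pain was the reason.
2. **Data processing.** State that a flexion not completed because of pain counts as available data. It enters the primary Mann-Whitney analysis at one single value, the worst rank (100 mm). Any VAS marked for the attempt is used only in a sensitivity analysis, so no patient has two primary values. A score absent for another reason stays missing and is described as such.
3. **Secondary end points.** State that the same rule applies at each time point in the flexion AUC for 1-8 hours.

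**Cost.** Two tick boxes on the case report form and a few sentences of text, with no new procedure and no change to eligibility. The downside is that 100 mm is then assigned and not stated by the patient, so any reported mean difference must name the worst-rank rule.

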###### **Secondary end points**

- Pain score with 45 degree active flexion of the knee (VAS) 1, 2, 4, 6 and 8 hours postoperatively, given as "area under curve" (AUC) calculation for the period 1-8 hours postoperatively.
- Pain score with 45 degree active flexion of the knee (VAS) 24 hours postoperatively.
- Pain score at rest (VAS) 1, 2, 4, 6 and 8 hours postoperatively, indicated as "area under curve" (AUC) calculation for the period 1-8 hours postoperatively.
- Pain score at rest (VAS) 24 hours postoperatively.
- Total need for morphine in the periods 0-8, 8-24 and 0-24 hours postoperatively, administered as patient controlled pain treatment (bolus 2.5 mg, lockout 10 minutes).
- Degree of nausea 1, 2, 4, 6 and 8 hours postoperatively, calculated as an average value for the period 1-8 hours postoperatively.
- Degree of nausea 24 hours postoperatively.
- Number of vomiting events during the periods 0-8, 8-24 and 0-24 hours postoperatively.
- Consumption of Zofran in the periods 0-8, 8-24 and 0-24 hours postoperatively.
- Degree of sedation 1, 2, 4, 6 and 8 hours postoperatively, calculated as an average value for the period 1-8 hours postoperatively.
- Degree of sedation 24 hours postoperatively.

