# **METHODOLOGY**

## **General treatment plan and medication dosage**

- An examination is made of whether the patient meets the inclusion and exclusion criteria.
- The trial period is 24 hours with T0 = last suture.
- **Standard pre-medication:**
  - 1 hour before arrival in the operating theatre: Paracetamol 1 g per os.
- **Ultrasound-guided insertion of catheter in the Adductor Canal:**
  - The catheter is inserted under ultrasound guidance under general anesthesia.
- **Treatment A**:
  - Adductor Canal Block via catheter inserted with ultrasound guide, with Ropivacaine 0.75%, bolus 30 ml 0 hours postoperatively, followed by bolus with Ropivacaine 0.75%, 15 ml 6 hours postoperatively. At 6 hours postoperatively an infusion catheter is connected with an infusion of Ropivacaine 0.2%, 9 ml per hour. The pump remains connected until the end of the trial 24 hours postoperatively.
- **Treatment B**:
  - Adductor Canal Block via catheter inserted with ultrasound guide, with placebo, isotonic NaCl, 30 ml bolus 0 hours postoperatively, followed by bolus of NaCl, 15 ml, 6 hours postoperatively. At 6 hours post-operatively an infusion catheter is connected with an infusion of isotonic NaCl, 9 ml per hour. The pump remains connected until the end of the trial 24 hours postoperatively.
- **Standard anaesthesia:**
  - General anaesthesia with Propofol and Remifentanil
  - Rocuron 0.5 mg/kg for intubation, no reversal with neostigmine
  - With a fall in blood pressure, ephedrine is given, alternatively metaoxedrin
  - Fluids as needed
  - 30 minutes before the end of anaesthesia, morphine 0.2 mg/kg is given iv
- **Standard postoperative nausea and pain treatment:**
  - Given postoperatively and for the rest of the 24-hour trials starting T0 + 2 hours:
    - Paracetamol 1 g every 6 hours po.
    - Ibuprofen 400 mg every 6 hour if there are no contraindications.
  - Patient-controlled iv morphine (PCA), bolus 2.0 mg, lockout time 15 minutes. Mixture: Morphine 1 mg/ml.
  - In the first hour postoperatively upon declaration of pronounced pain, fentanyl 0.1 mg may be given iv. The dose may be repeated after 10 minutes.
  - If there is a need for additional morphine in addition to the PCA pump, in the first 2 hours postoperatively, bolus doses of 2.5 mg morphine iv can be given on request.
  - Patients who are in regular opioid therapy preoperatively continue this treatment unchanged during the period of the trial.

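### The total-morphine endpoint counts only PCA doses, so the 0-8 h and 0-24 h totals omit the rescue morphine and fentanyl that the protocol allows in the first two hours

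*Protocol*

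**What the plan says.** Under Secondary end points, the protocol sets the endpoint as "Total need for morphine in the periods 0-8, 8-24 and 0-24 hours postoperatively" and then restricts it to what is "administered as patient controlled pain treatment".

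Under Clinical assessments, the measurement follows that restriction. The item on patient-controlled consumption has two entries: "Number of bolus doses delivered in the period 0-8 hours postoperatively is recorded" and "Number of bolus doses delivered in the period 0-24 hours postoperatively is recorded".

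Under General treatment plan and medication dosage, two iv opioids are allowed outside the pump after surgery:

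- Fentanyl: "In the first hour postoperatively upon declaration of pronounced pain, fentanyl 0.1 mg may be given iv". It adds: "The dose may be repeated after 10 minutes".
- Morphine: "If there is a need for additional morphine in addition to the PCA pump", then "in the first 2 hours postoperatively, bolus doses of 2.5 mg morphine iv can be given on request". No maximum number of boluses is stated.

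The section Other treatment has all other medical treatment recorded on the case report form. The section Case Report Forms lists the medication and observation form among the source data. No section adds the rescue doses to an endpoint or makes rescue use an endpoint of its own.

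**The concern.** The endpoint's name and its definition disagree. On-request morphine is morphine, it is given after surgery, and it falls inside the 0-8 h and 0-24 h windows, yet it is left out of a quantity called total need for morphine. This needs no conversion factor and no assumption about the arms. Fentanyl is a separate matter. Leaving it out does not contradict a label that speaks of morphine, but it does leave out opioid that the patient received for the same pain.

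The Aim section puts reduced postoperative morphine use first in the trial's hypothesis and does not limit it to pump use. Both rescue drugs are given in response to pain or a request, so the uncounted amount may depend on treatment. The section on considerations for the study as a whole expects better pain management in the ropivacaine group. If that is right, more opioid goes uncounted on placebo and the comparison moves toward no difference.

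**Working it through.** **1. What the endpoint counts, by window**

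| Source of opioid | When allowed | In 0-8 h | In 8-24 h | In 0-24 h | Counted |
|---|---|---|---|---|---|
| PCA morphine | Throughout | Yes | Yes | Yes | Yes |
| On-request iv morphine, 2.5 mg | First 2 h | Yes | No | Yes | No |
| iv fentanyl, 0.1 mg, repeatable | First hour | Yes | No | Yes | No |

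The direct undercount is therefore confined to the 0-8 h and 0-24 h totals.

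**2. The plan's own powered figure, for context.** The sample size rests on pain score (difference 20, SD 20, 5% type 1 and 20% type 2 risk; two-sided assumed). The normal approximation gives 2 × (1.96 + 0.84)² × (20/20)² = 15.7, so 16 per group. The two-sample t-test gives 16.7, so 17 per group and 34 in total, with 80.7% power. The stated 34 is reproduced, and opioid counting does not enter it.

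**3. Uncounted opioid in one patient.** The documents give no fentanyl conversion. I assume 50 to 100 mg iv morphine per mg fentanyl.

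- One on-request bolus: 2.5 mg.
- One fentanyl dose: 0.1 × 50 = 5 mg to 0.1 × 100 = 10 mg.
- Two fentanyl doses and two boluses: 10 + 5 = 15 mg to 20 + 5 = 25 mg.

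**4. Pump ceiling, for scale.** The protocol gives two settings, so there are two ceilings.

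- 2.0 mg with 15-minute lockout (treatment plan): 60/15 × 2.0 = 8 mg/h, or 16 mg in 2 h.
- 2.5 mg with 10-minute lockout (endpoint text): 60/10 × 2.5 = 15 mg/h, or 30 mg in 2 h.

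One 2.5 mg rescue bolus equals 1.25 pump boluses under the first setting and 1.0 under the second. The same bolus count differs by 25% in mg (2.5/2.0 = 1.25) depending on which setting is used.

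**5. Between-arm difference lost.** Loss = (placebo rescue use − active rescue use) × opioid per rescued patient. Rescue rates are not in the documents, so every row rests on an assumption.

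| Assumed rescue use | Calculation | Difference lost |
|---|---|---|
| 50% in both arms, one fentanyl dose and one bolus | (0.5 − 0.5) × 7.5 to 12.5 mg | 0 mg |
| 60% placebo, 30% active, one fentanyl dose and one bolus | 0.3 × 7.5 to 0.3 × 12.5 mg | 2.25 to 3.75 mg |
| Placebo averages 2 to 4 more boluses, fentanyl not counted | 2 × 2.5 to 4 × 2.5 mg | 5 to 10 mg |

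In the second row only 0.3 × 2.5 = 0.75 mg of the loss is morphine; the rest comes from fentanyl and depends on the assumed conversion. In the first row each arm still has 0.5 × 7.5 = 3.75 to 0.5 × 12.5 = 6.25 mg per patient uncounted. The totals are then too low, although their difference is not distorted.

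**The case against.** PCA consumption is explicitly defined and matches how it is recorded. With rescue doses on the case report form, they could be reported by arm without touching the endpoint. That stands as a workable minimum. It does not repair an endpoint called a total that excludes part of the morphine. Nor is this a detail left for a statistical analysis plan, because the protocol itself fixes both the definition and the measurement.

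This is also one of eleven secondary endpoint items, and a bias toward no difference would not create a false claim of benefit. Both points stand and limit the weight of the finding.

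A reader might go further and infer that the comparison is shown to be biased by 5-10 mg. The documents do not support this. They give no rescue rates, the arm imbalance is an inference from the rescue triggers and the stated expectation, and the loss is zero if rescue use is equal.

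A reader might also argue that the lockout pushes surplus demand on placebo into uncounted rescue, or that rescue lowers later pump use. Either is plausible, but the documents establish neither. The first argument is also weaker under the endpoint text's pump setting, where the ceiling is 15 rather than 8 mg/h.

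**Conclusion.** The point holds as a mismatch of definition. As written, the 0-8 h and 0-24 h totals omit on-request morphine and rescue fentanyl and so understate opioid use in any patient who receives them. The omission itself is certain from the text.

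A bias toward no difference is probable, provided that rescue use follows pain and pain is worse on placebo. Its size cannot be derived from the protocol. It is 0 mg with equal rescue use, about 2-4 mg morphine equivalent under the 60% v 30% assumption with a 50-100 conversion, and 5-10 mg if placebo patients average 2-4 more boluses.

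The endpoint should be corrected, but the finding does not bear on the primary endpoint or on the 34 patients.

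**What to change.** - In Secondary end points and in Clinical assessments, define the endpoint as total postoperative opioid over 0-8, 8-24 and 0-24 h in iv morphine equivalents: PCA morphine plus supplementary morphine plus fentanyl.
- Fix the fentanyl conversion factor before unblinding and add a sensitivity analysis over its plausible range.
- Keep PCA-only consumption as a supporting analysis. Report continued preoperative opioids separately.
- Reconcile the PCA settings in Secondary end points and in the treatment plan, which differ in bolus and lockout, before bolus counts are converted to mg.

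The cost is a change of wording in two sections and an agreed conversion factor, which the documents do not supply. Over the assumed range that factor doubles the fentanyl contribution, hence the sensitivity analysis. No new data collection should be needed if rescue doses are recorded on the case report form as the protocol requires, and the sample size does not change.

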## **Blinding procedure, packaging and labeling**

## **Blinding procedure, packaging and labeling**

The study is performed as a double-blind randomized study. Randomisation will be performed by the Capital Region Pharmacy. The experimental medicine will be packed and labelled by the Capital Region Pharmacy. in accordance with the rules for this. Each patient receives medication as indicated below under **"General treatment plan and medication dosage"**. Ropivacaine 0.75% or placebo are blinded by being packaged in one blinded closed cardboard box. The cardboard box is handed over to a person not involved in the trial, who records the batch number and expiry date. This person then draws the medicine into a neutral spray and returns it to the patient's anaesthesia personnel for administration. 2 sets of additional sealed code envelopes are prepared. These contain information about which treatment each of the subjects is being randomly assigned. One set is retained by the sponsor, while the other is retained by the investigator at the Department of Anaesthesia, HOC, Rigshospitalet, in a secure locked place. Capital Region Pharmacy retains the non-blinded randomization list, which will only be sent to the investigator when the data has been analysed.

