## **Other treatment**

Other medications that are considered necessary for the subject will be given at the discretion of the investigator.

Administration of all other medical treatment will be recorded on the accompanying Case Report Form.

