## **Case Report Forms**

A Case Report Form (CRF) will be completed for each patient included in the study. This will be signed by the investigator to confirm the accuracy of the data. Corrections to the data will only be made by crossing out the incorrect data (the incorrect information will remain visible and legible) with the correct data written next to the deleted data. Correction fluid will not be used. Corrections will be dated and signed by the investigator or their deputy.

Source data is defined as: CRF, health records, medication and observation form from the intermediate unit and anesthesia record.

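### The protocol gives two incompatible PCA morphine settings: 2.5 mg with a 10-minute lockout in the secondary endpoint, 2.0 mg with a 15-minute lockout in the treatment plan

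*Protocol*

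**What the plan says.** Three places in the protocol matter.

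- **Secondary end points.** Total morphine need over 0-8, 8-24 and 0-24 hours is an endpoint, with the drug "administered as patient controlled pain treatment (bolus 2.5 mg, lockout 10 minutes").
- **General treatment plan and medication dosage.** The pump order for all patients reads "Patient-controlled iv morphine (PCA), bolus 2.0 mg, lockout time 15 minutes. Mixture: Morphine 1 mg/ml". The same section also allows staff to give extra morphine early on: "bolus doses of 2.5 mg morphine iv can be given on request". This extra dose is limited to the first 2 hours, comes on top of the pump and has no lockout.
- **Clinical assessments.** PCA consumption is captured as counts, for 0-8 hours and again for the full trial period: "Number of bolus doses delivered in the period 0-24 hours postoperatively is recorded". No milligram or volume reading is listed there.

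Two other statements bear on how the delivered dose might be recovered. Under Other treatment: "Administration of all other medical treatment will be recorded on the accompanying Case Report Form". Under Case Report Forms: "Source data is defined as: CRF, health records, medication and observation form from the intermediate unit and anesthesia record".

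**The concern.** A pump can run only one of these settings, so one of the two statements is wrong as written. This matters in two ways.

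The first is the opioid prescription itself. The Background describes a largely elderly population with much co-morbidity. The treatment plan already gives these patients morphine 0.2 mg/kg before the end of anaesthesia, allows fentanyl and extra morphine after surgery, and continues any regular preoperative opioid. Ward staff and ethics reviewers should find a single bolus and a single lockout.

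The second is the scale of a secondary endpoint. Lower morphine use is the first effect named in the hypothesis under Aim. If milligrams are built from bolus counts, a bolus size has to be supplied, and the endpoint definition supplies 2.5 mg while the dosing section supplies 2.0 mg. Data processing calls for means, standard deviations, medians and quartiles. In milligrams, all of these scale with the bolus size chosen.

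**Working it through.** **Inputs.** Setting E (Secondary end points): bolus 2.5 mg, lockout 10 min. Setting T (General treatment plan): bolus 2.0 mg, lockout 15 min. Recorded quantity (Clinical assessments): number of boluses delivered.

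The protocol states no hourly maximum and no conversion to milligrams, so it has no figure of its own on this point to reproduce. The sample size is outside the question: it rests on a VAS difference of 20 with SD 20 and uses no morphine figure. It does reproduce. A two-sample t-test, taken as two-sided, at 5% and 80% power needs 16.7 per group, hence 17 per group and 34 in total.

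**Step 1: can the two statements be reconciled?** Both are current text and both apply to all patients after surgery. Neither is tied to a particular period, arm or subgroup. The 2.5 mg dose given on request in the treatment plan is not the PCA setting, because it is separate from the pump, has no lockout and stops after 2 hours. Since both bolus and lockout differ, a single mistyped digit does not explain the conflict.

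**Step 2: theoretical pump ceiling.** Maximum rate = bolus × 60 / lockout.

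| | Setting E | Setting T |
|---|---|---|
| Rate | 2.5 × 60/10 = 15 mg/h | 2.0 × 60/15 = 8 mg/h |
| 0-8 h | 15 × 8 = 120 mg | 8 × 8 = 64 mg |
| 0-24 h | 15 × 24 = 360 mg | 8 × 24 = 192 mg |

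Ratio: 15 / 8 = 1.875. These are limits reached only if every lockout interval is used. They are not expected doses.

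**Step 3: error in milligrams derived from counts.** Derived mg = count × assumed bolus; true mg = count × programmed bolus. The relative error is assumed/programmed − 1.

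- Assume 2.5, pumps at 2.0: 2.5/2.0 − 1 = +25%.
- Assume 2.0, pumps at 2.5: 2.0/2.5 − 1 = −20%.
- Assume the programmed bolus: 0%.

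The same factor applies to each arm's PCA mean and median and to the difference between arms in milligrams.

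**Step 4: what does not change.** Let all pumps run one setting, let *k* be the bolus size applied, and let *a* and *b* be the arm summaries in boluses. The percent difference is (*ka* − *kb*)/(*kb*) = (*a* − *b*)/*b*, which is free of *k*. Ranks are also unchanged by a common positive factor, so the Mann-Whitney p-value is the same.

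This invariance has two limits. It covers PCA morphine alone: if the extra morphine given outside the pump is added in milligrams, a wrong *k* changes the weight of one component and no longer acts as a common factor. It also assumes one setting throughout: if pumps were set differently between patients, the bolus counts themselves would not be comparable.

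**The case against.** The strongest reply is that the two statements do not carry equal weight. The treatment plan is the dosing section and gives a complete order with bolus, lockout and concentration. In the endpoint list the setting is only a parenthesis describing how the measured drug is given. Staff programming a pump would normally work from the former. This stands as a reason to think 2.0 mg with a 15-minute lockout was intended, and it lowers the likely harm. It remains an inference, because the protocol states no rule of precedence. Two sentences might be read as pointing to the treatment plan, "Each patient receives medication as indicated below under" (in the blinding section) and "The patient receives the above treatments in accordance with a computer-generated randomized list" (closing Clinical assessments). They concern the blinded study drug and the randomised treatments, however, and PCA morphine is common to both arms, so they are weak support. Even if the treatment plan governs, the endpoint text is then wrong and needs correcting.

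The second reply is that the milligram error is conditional. It needs milligrams to be derived from counts, the wrong bolus size to be applied, and nobody to check the pump setting or source records. That is also correct: +25% and −20% are the errors in two specific cases, not an expected bias. The medication and observation form, the CRF entry for other treatment and the 1 mg/ml concentration are possible routes to the delivered dose. None of them states that the programmed bolus or the infused PCA volume is recorded.

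The third reply is that the inference is untouched. For PCA morphine under one uniform setting this stands in full, as step 4 of the working shows.

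**Conclusion.** The contradiction is real and the protocol does not resolve it. It covers both bolus and lockout and implies theoretical ceilings of 15 and 8 mg/h. The effect on reported PCA milligrams is +25%, −20% or nil, depending on which bolus was programmed and which was used for conversion; the protocol does not show which case applies. These error figures assume that milligrams are derived from the recorded bolus counts.

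The point should be fixed because it concerns an opioid dosing instruction and the absolute scale of a secondary endpoint. It goes no further than that. The primary endpoint (VAS on 45-degree flexion at 4 hours) and the sample size of 34 are unaffected. So are the p-value and percent difference for PCA morphine, provided all pumps ran the same setting.

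**What to change.** The investigators should confirm which PCA setting was intended, probably bolus 2.0 mg with a 15-minute lockout as in the treatment plan. They should then state it identically under Secondary end points and under General treatment plan and medication dosage. PCA morphine in milligrams should be computed as the recorded bolus count times the bolus size actually programmed on that patient's pump.

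The cost is a one-line correction in the endpoint list, or in the treatment plan if the other setting was meant. Design, sample size and statistical test stay as they are.
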